## Abstract

**Background:**

Dual-method use is known as the most reliable protection against unintended pregnancies and sexually transmitted infections, including HIV. However, it is not commonly used in sub-Sharan Africa, especially among women using highly effective contraceptives. This article describes a protocol to evaluate the effect of an intervention formulated under the positive deviance approach for promoting dual-method use in Uganda.

**Methods:**

A total of 150 women will be interviewed using a structured questionnaire to find those practicing dual-method use. In-depth interviews will then be conducted with all women using the dual method and 10 women using only highly effective contraceptives to identify their unique practice. Then, a cluster randomized controlled trial will be conducted to examine the effect of an intervention formulated under the positive deviance approach on dual-method uptake and adherence. Twenty health facilities will be randomized to an intervention or control arm and 480 women will be enrolled in each group. The participants will be followed up for 8 months.

**Discussion:**

This trial focuses on women who already adapted dual-method use and identifies their unique solutions to promote dual-method use. This trial could tackle barriers for dual-method use, which expert outsiders may fail to recognize, by analyzing and promulgating their unique behaviors. This study could provide evidence that the positive deviance approach can address unintended pregnancies and sexually transmitted infections as well as other health problems which usual approaches have failed to address.

**Trial registration:**

UMIN-CTR Clinical Trial, UMIN000037065. Registered on 14 June 2019.

## Background

In sub-Saharan Africa (SSA), women of reproductive age bear a disproportionate burden of unintended pregnancies and sexually transmitted infections (STIs) including human immunodeficiency virus (HIV) [1]. In SSA, an estimated 29% of pregnancies are unintended [2]. Moreover, women account for approximately 56% of all adults living with HIV in this region [3]. This gender disparity starts when women reach their reproductive age, and women represent 59% of new HIV infections in this region [3, 4].

Unintended pregnancies occur because appropriate methods of contraception are not available or avoided [5]. To prevent this, highly effective contraceptives (HECs), such as hormonal contraceptives (e.g. pills, injectables, and implants), non-hormonal intrauterine device (IUD), and sterilization, were introduced to family planning programs [5]. In many countries in SSA, women have started to use these methods more frequently in recent decades [6]. HECs are effective in preventing unintended pregnancies but cannot prevent HIV/STIs [7]. Therefore, women need to protect themselves from HIV/STIs, regardless of whether they are using HECs or not.

Dual protection is defined as protection against the dual risks of unintended pregnancies and HIV/STIs [8]. It can be accomplished by either using a condom consistently alone or with HECs (dual-method use) [8]. Condoms are an effective method for women of preventing HIV/STIs from their sexual partners [9]. However, as they are often used incorrectly and inconsistently, condoms can only prevent 85% of pregnancies [10]. Dual-method use, thus, has been recommended as the most reliable protection against the dual risks in couples who do not want a child or who want to delay childbirth [7, 8, 11, 12]. Nevertheless, it remains uncommon [11]. In the United States, 7% of reproductive-age women who were sexually active used this method [13]. In SSA, most research has focused on dual-method use among women living with HIV and adolescents. For instance, 16% and 39% of women living with HIV practiced dual-method in 3 months in Ethiopia and Kenya, respectively [8, 14], while 7% of South African adolescents aged 15–24 years reported dual-method use [15].

A trade-off between HEC and use of condoms is a barrier to practicing dual protection. Women are less likely to use condoms with their male partners when using HECs [16]. Use of condoms may become unacceptable, especially in marital sex, as it is perceived as protection against HIV/STIs rather than pregnancies. Both women and men may think condoms are unnecessary with an intimate partner, especially when women are using HECs. However, use of condoms is necessary for women who are at risk of HIV/STIs, regardless of use of HEC [17, 18]. Extramarital sexual relationships are common, especially among men, in SSA [19]. For instance, an estimated 44% of HIV infections occurred among married or cohabiting couples in Kenya [20].

Several interventions have been conducted to promote dual-method use in the USA [11, 12]. However, few interventions had a significant effect on dual-method use [11, 12, 21] and the impact of such interventions was often not sustainable [22]. In resource-limited settings, including SSA, no interventions have been examined, although people are at considerable risk of unintended pregnancies and HIV/ STIs [11]. Women and men may perceive the importance of the use of condoms for preventing HIV/STIs, but often do not practice it [23]. Motivating factors for dual-method use remain unknown when the percentage of such users is low.

The positive deviance approach has the potential to address barriers to sensitive issues such as sexual and reproductive health. This approach seeks behaviors that contribute to otherwise high-risk individuals, or positive deviants, remaining free from a disease or condition and enables communities to adopt such practices [24, 25]. This approach has addressed complex development challenges, which are often hard for expert outsiders to measure, such as gender-related and socio-cultural barriers [24]. For example, the positive deviance approach was applied to advocate against female genital mutilation using actual words of positive deviants in Egypt [24]. Use of condoms is not prevalent in SSA, especially among married women using HECs. Barriers to condom use are complex and it is often difficult for outsiders to grasp the whole picture [26]. Given the limited effect of previous interventions [11], the positive deviance approach could be an ideal option for promoting dual-method use.

The present article illustrates a study protocol to examine the effect of an intervention formulated under the positive deviance approach on dual-method use among married women using HECs with their partners in Uganda.

## Methods

### Study setting

The present study is conducted in Mbarara district, south-western Uganda. Use of contraceptives has significantly increased in Uganda. Its use among married women increased from 14% in 2001 to 35% in 2014 [27]. Like other countries in SSA, HECs are becoming the norm in Uganda, with 32% of currently married women using them in 2014 [27]. Injectables are the most used method (19%) followed by implants (6%), female sterilization (3%), pills (2%), and IUD (2%) [27]. Despite the significant increase in the use of contraceptives, an estimated 46% of pregnancies were unintended in Uganda in 2018 [28]. The prevalence of HIV among adults aged 15–64 years is 6.2% and is higher among women (7.6%) than among men (4.7%) [29]. The south-west region had the second highest prevalence of HIV (7.9%) after the Central region (8.0%) in Uganda [29].

Mbarara district has one regional hospital, six general hospitals, four county-level health centers (health center IV), 14 sub-county-level health centers (health center III), and 37 parish-level health centers (health center II) [30]. Among them, 48 are public health facilities and 23 facilities are located in urban areas [30]. A family planning service is provided for free at all levels of health centers. Male and female condoms are also provided free by the Ministry of Health and by local and international non-governmental organizations [31]. Condoms can also be purchased from supermarkets and pharmacies for US$0.15–US$0.50 [31].

### Study objectives

The objectives of the present study are: (1) to identify unique behaviors that are common only among married women who practice dual-method use with their partners in an HIV-prevalent setting in Uganda; and (2) to evaluate the effect of an intervention formulated under the positive deviance approach for promoting dual-method use among married women using HECs.

### Study design

The present study consists of Phases I and II. In Phase I, eligible women will be screened with a structured questionnaire. In-depth interviews will then be conducted with all women practicing dual-method use and 10 women using only HECs to identify the unique practice that is common only among women practicing dual-method use (positive deviants). In Phase II, a cluster randomized controlled trial (C-RCT) will be conducted to assess an intervention formulated under the positive deviance approach for promoting dual-method use. The intervention will consist of clinic-based and phone counseling and a participatory workshop that will be tailored based on the unique practice identified in Phase I. The overall study flow chart is shown in Fig. 1. The schedule of the C-RCT is shown in the Standard Protocol Items: Recommendations for Intervention Trials (SPIRIT) figure (Fig. 2). The SPIRIT checklist is provided in Additional file 1.

**Fig. 1 Fig1:**
[figure not shown]
Study flow chart

**Fig. 2 Fig2:**
[figure not shown]
SPIRIT figure

#### Phase I: identify positive deviants

##### Sample size, eligibility, and recruitment

In Phase I, 150 women will be interviewed. This is based on the assumption that at least 7% of women would practice dual-method use [13] and at least 10 women who are considered as a positive deviant would be identified.

To be eligible for joining this study, participants should have the following characteristics: (1) women; (2) aged 18–49 years; (3) sexually active; (4) using HECs at the time of recruitment; (5) have a desire to avoid pregnancy for 12 months from recruitment; (6) have a husband or live-in sexual partner; and (7) have access to a valid phone number.

Being sexually active is defined as having had sexual intercourse in the 3 months before the study [13]. Pregnant women and women who are infertile for other reasons will be excluded from this study. Health workers, including community health workers, political and religious leaders, and teachers will also be excluded because they may not represent communities or be influenced by their occupations and social status.

For sampling, five health facilities will be selected purposively. Then, five trained female research assistants will approach female clients in the family planning sections of the selected health facilities. The first client will be selected randomly at each clinic and then every third client will be informed about the opportunity to participate in this study. If they are interested in participating, the research assistants will ask screening questions using a pretested questionnaire to check their eligibility for the study. This process will be repeated until the required sample size is met.

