##### Data collection

The five female trained research assistants will conduct face-to-face interviews using a pretested structured questionnaire with the participants. These interviews aim to identify women practicing dual-method use and their basic sociodemographic characteristics. Data collection items include basic sociodemographic characteristics, the types of HECs, the frequency of condom use in the past 2 months, and the histories of unintended pregnancies and diagnosed HIV/STIs. Women using both HECs and condom always will be regarded as practicing dual-method use. Dual-method users without no reported histories of unintended pregnancies and HIV/STIs will be considered as positive deviants.

Next, in-depth interviews will be conducted by the research assistants with all positive deviants to identify their unique practice, such as effective communication for use of condoms that is actually working. Then, 10 women who do not practice dual-method use will be randomly selected for in-depth interviews to document common practices and verify if the practice identified in positive deviants is unique. The interviews will be open-ended and an interview guide will be used. The interview guide focuses on the following domains: (1) perceptions of condom use and contraception; (2) reasons and motivations for condom use or non-use; (3) negotiation and communication for condom use; and (4) risk perceptions for or unintended pregnancy and HIV/STIs.

The data collection tools were first developed in English and then translated to Runyankore by an independent researcher. They were back-translated to English by the Ugandan researcher (SM) to ensure the accuracy of the translation. All interviews will be conducted in either English or Runyankore. In-depth interviews will be audio recorded based on the consent of participants. All participants will be given some commodities worth 10,000 Ugandan Shillings (UGX) (equivalent to US$3) after the initial interview; those who participate in the in-depth interview will receive 10,000 UGX for their time and transportation.

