The present study has several limitations. First, the success of the positive deviance approach depends on whether women practicing dual-method use or positive deviants can be found in the study area [24, 48]. Considering the prevalence of such people, the sample size can be too small and may need to be modified. Second, positive deviants are identified by the research team not by community members in this trial. Therefore, the effect of the intervention can be limited in mobilizing and empowering communities to adopt identified strategies, compared to the usual approach including self-discovery of positive deviants [24, 48]. Third, high attrition is anticipated, especially among women in the control arm, as all the interventions and follow-ups after recruitment and initial counseling are phone-based [11]. The present trial, therefore, calculated the sample size considering a relatively high attrition rate to offset potential losses to follow-up. Moreover, it will be minimized by building rapport with participants. For this, each participant will be contacted by the same positive deviant and/or research assistant for counseling and follow-up throughout the study period. Fourth, the outcomes will be assessed based on self-reports from participants and thus subject to response bias. Dual-method use can be over-reported while the incidence of STIs and unintended pregnancies can be under-reported due to social desirability bias. However, response bias will be minimized by assuring each participant of confidentiality of responses at the enrollment. Lastly, findings of the present study might lack external validity to other locations as it will focus on one particular community under the positive deviance approach [48]. In the present study, participants will be recruited in only public health facilities; thus, findings from this study may not be generalized to all women using HECs. To apply findings and the interventions developed in the present study to other areas and populations, further research will be necessary to assess its effectiveness in a given context.

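### Phase I's 150 women are expected to give about 10 dual-method users, not the stated 10 positive deviants, whom the plan defines as a smaller group

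*Protocol article*

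**What the plan says.** In the Phase I section on sample size, eligibility and recruitment, the protocol article states "In Phase I, 150 women will be interviewed". It gives two grounds: that "at least 7% of women would practice dual-method use", and that "at least 10 women who are considered as a positive deviant would be identified". No other rate enters. Recruitment at the clinics continues until the required sample size is reached, so it stops on women interviewed and not on positive deviants found.

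The Phase I data collection section then sets two nested definitions. First, "Women using both HECs and condom always will be regarded as practicing dual-method use". Second, "Dual-method users without no reported histories of unintended pregnancies and HIV/STIs will be considered as positive deviants". The double negative in the second sentence can only sensibly be read as requiring no such history. In that section, in-depth interviews are held with all positive deviants and with 10 randomly selected women who do not practise dual-method use.

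The study design section says something different: "In-depth interviews will then be conducted with all women practicing dual-method use and 10 women using only HECs". It labels the dual-method users as the positive deviants, with no condition on history. The abstract also plans to interview all dual-method users.

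The limitations in the Discussion concede that, given how common such women are, "the sample size can be too small and may need to be modified".

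**The concern.** The sample size statement takes a rate for one group and attaches the result to a smaller one. The 7% is a rate of dual-method use, while the target of 10 is for positive deviants, who must also pass a filter on history. No allowance is made for that filter, and the margin is only half a woman (10.5 against 10).

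The two definitions also change who is interviewed. A dual-method user with a past unintended pregnancy is interviewed as a positive deviant under the study design section. Under the data collection section she is neither a positive deviant nor a non-user, and so falls outside both interview groups.

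Positive deviants carry the approach under test. Their practices supply the content of the intervention, they help to facilitate the workshop, and they are assigned the telephone counselling at 3, 5 and 7 months. A reader planning Phase II from the stated yield would expect more of them than the plan's own assumption delivers.

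**Working it through.** **Inputs.** N = 150 women, p = 7% dual-method use (stated as a minimum) and a target of 10 positive deviants, all from the Phase I sample size section. q is the share of dual-method users with no reported history of unintended pregnancy or HIV/STI. The documents do not give q, so it is an assumption here and is shown over a range.

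**Reproducing the plan's figure.** N × p = 150 × 0.07 = 10.5. In the other direction, 10 / 0.07 = 142.9, so 143 women, which rounds up to 150. The stated size is therefore recovered using dual-method use alone, which is the case q = 1.

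**Break-even.** With the filter, the expected number of positive deviants is 150 × 0.07 × q = 10.5q. This equals 10 at q = 10 / 10.5 = 0.952. The expected yield is below 10 once more than 1 − 0.952 = 4.8% of dual-method users are excluded.

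**Range over q.** Four quantities follow:
- expected yield = 10.5q
- chance of at least 10 = P(X ≥ 10) for X ~ Binomial(150, 0.07q), exact
- N for an expected 10 = 10 / (0.07q)
- dual-method prevalence at which 150 women give an expected 10 = 10 / (150q)

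| q (assumed) | Expected from 150 | P(at least 10) | N for expected 10 | Prevalence needed |
|---|---|---|---|---|
| 1.00 | 10.5 | 0.61 | 143 | 6.7% |
| 0.95 | 9.98 | 0.54 | 151 | 7.0% |
| 0.80 | 8.40 | 0.33 | 179 | 8.3% |
| 0.70 | 7.35 | 0.20 | 205 | 9.5% |
| 0.50 | 5.25 | 0.04 | 286 | 13.3% |

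The first row is the plan's implicit case. The second to fourth columns hold p at exactly 7%; the last column lets p vary and holds N at 150.

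**The case against.** The strongest reply is that 7% is worded as a floor. The probabilities above fix prevalence at the least favourable value that the plan assumes, and a modestly higher rate would restore the target: 8.3% at q = 0.8, or 9.5% at q = 0.7. The background section also cites higher rates in the region, 16% in Ethiopia and 39% in Kenya. This stands as a limit on the size of the point, but the article does not make the argument. The higher rates come from women living with HIV, who would fail the history criterion.

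A second reply is that the study design section equates dual-method users with positive deviants, and on that reading the arithmetic is consistent. This is true, but the data collection section gives the operative definition and contradicts it. The reply therefore restates the inconsistency.

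A third is that the limitations already admit that the sample may be too small. They do so in general terms and do not mention the history filter. That the article gives no rule for enlarging the sample is not held against it, since the full protocol may contain one.

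Finally, Phase I feeds open-ended interviews and tests no hypothesis. Nothing in the article says that it fails with seven or eight positive deviants. That is fair, and the probability of reaching 10 should be read as a description of the stated yield and not as a power requirement.

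Two stronger readings are tempting and should be resisted. A reader might take the study setting's statement that "an estimated 46% of pregnancies were unintended in Uganda in 2018" as evidence that about half of dual-method users would be excluded. That figure is a share of pregnancies, not of women, and says nothing about women who use condoms consistently with a highly effective method. A reader might also divide the intervention arm's counselling calls by a small number of positive deviants and infer an unworkable load. The article sets no limit on calls per caller, and its limitations section allows a positive deviant and/or a research assistant to be each participant's contact for counselling and follow-up.

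**Conclusion.** The point holds as an error in the stated yield. At the plan's minimum of 7%, 150 women are expected to give 10.5 dual-method users, and fewer than 10 positive deviants unless at least 95.2% of those users have a clear history. The direction does not depend on any assumption about q, because the definition can only remove women. The size does: it rests on an assumed q and on prevalence being exactly 7%. The yields of 5.25 to 9.98 are illustrations over a range, not estimates. The conflict over who counts as a positive deviant, and who is interviewed in depth, is in the text and needs no assumption.

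The consequence is confined to Phase I and to the women available to shape and deliver the intervention. The Phase II sample size calculation does not use this figure.

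**What to change.** 1. Restate the Phase I yield: at 7% dual-method use, 150 women give about 10 dual-method users and fewer positive deviants, with the range over the assumed qualifying share. Alternatively, keep the target of 10 and state the dual-method prevalence that it requires at a stated qualifying share.
2. Use one definition of positive deviant. Reconcile the abstract and the study design section, where all dual-method users are interviewed, with the data collection section, where only positive deviants are. State what happens to dual-method users who have a relevant history.
3. Correct the double negative in the definition.

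These changes cost only rewording.

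As an option, not a requirement, screening could continue until 10 women meet the full definition, up to a stated cap. At 7% this means an expected 143 screening interviews if all dual-method users qualify, 205 if 70% do and 286 if half do. The cost is therefore more short interviews and more time before Phase II.

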##### Data collection

The five female trained research assistants will conduct face-to-face interviews using a pretested structured questionnaire with the participants. These interviews aim to identify women practicing dual-method use and their basic sociodemographic characteristics. Data collection items include basic sociodemographic characteristics, the types of HECs, the frequency of condom use in the past 2 months, and the histories of unintended pregnancies and diagnosed HIV/STIs. Women using both HECs and condom always will be regarded as practicing dual-method use. Dual-method users without no reported histories of unintended pregnancies and HIV/STIs will be considered as positive deviants.

Next, in-depth interviews will be conducted by the research assistants with all positive deviants to identify their unique practice, such as effective communication for use of condoms that is actually working. Then, 10 women who do not practice dual-method use will be randomly selected for in-depth interviews to document common practices and verify if the practice identified in positive deviants is unique. The interviews will be open-ended and an interview guide will be used. The interview guide focuses on the following domains: (1) perceptions of condom use and contraception; (2) reasons and motivations for condom use or non-use; (3) negotiation and communication for condom use; and (4) risk perceptions for or unintended pregnancy and HIV/STIs.

The data collection tools were first developed in English and then translated to Runyankore by an independent researcher. They were back-translated to English by the Ugandan researcher (SM) to ensure the accuracy of the translation. All interviews will be conducted in either English or Runyankore. In-depth interviews will be audio recorded based on the consent of participants. All participants will be given some commodities worth 10,000 Ugandan Shillings (UGX) (equivalent to US$3) after the initial interview; those who participate in the in-depth interview will receive 10,000 UGX for their time and transportation.

